### Intervention

For the verum, 20,000 IU (Dekristol® 20,000 I.E., Mibe GmbH Arzneimittel) or 2000 IU colecalciferol (two tablets Dekristol® 1000 I.E., Mibe Arzneimittel GmbH) are encapsulated and filled up with a mixture of mannitol and colloidal silicon dioxide (Füllstoff DAC). The placebo consists solely of the hard gelatine capsules with filler. To ensure blinding, verum and placebo capsules are indistinguishable regarding appearance, quantity, weight, and packaging.

Patients, who have consented to participate in the trial, are randomly allocated to either vitamin D_3_ or placebo for a total of 12 weeks (84 days).

#### *Intervention arm*

The vitamin D_3_ treatment consists of a personalized loading dose, followed by a daily maintenance dose of 2000 IU. Several clinical trials have highlighted that 25(OH)D levels, achieved by vitamin D_3_ intake, strongly depend on a person’s 25(OH)D level and weight at baseline [29–31]. In order to provide the trial participants with a sufficient vitamin D_3_ dose, an equation to calculate individual loading doses is applied. The equation includes the baseline 25(OH)D level and body mass index (BMI) [31]:

Loading dose = 165 * BMI [kg/m^2^] * (70 – baseline 25(OH)D level [nmol/L]).

The equation by Jansen et al. was developed to increase 25(OH)D levels to 80 nmol/L, which is slightly above the generally accepted optimal level of 75 nmol/L [32]. In order to avoid non-physiological high doses of vitamin D_3_, the loading dose will be distributed in daily doses of 20,000 IU, which resembles the maximum amount of vitamin D_3_ that can be naturally produced in the skin by sunbathing in a swimsuit on a summer day [33]. The reasons for this are not safety concerns but mechanistic considerations regarding the vitamin D_3_ metabolism: Unbound vitamin D_3_ in the serum is of major importance for effective vitamin D activity [34, 35]. Its bioavailability in turn is higher when doses are given on a daily basis while avoiding single high doses [34, 35].

However, if the total personalized vitamin D_3_ loading dose of a participant is exceptionally high, 2 × 20,000 IU/day will be administered at the beginning to ensure that the entire vitamin D_3_ loading dose is administered within the first 11 days, while the patient is still in the rehabilitation clinic (for safety reasons). Accordingly, the maximum achievable loading dose of vitamin D_3_ is fixed at 420,000 IU over 11 days. This dose would only be necessary for an individual with a 25(OH)D level of 5 nmol/L (lowest expected baseline level) and a BMI of 40 kg/m^2^ (maximum possible BMI in this trial since patients with BMI > 40 kg/m^2^ are excluded). After administrating the last loading dose capsule, patients will continue with the maintenance dose on the next day until the end of the intervention (day 84). The daily maintenance dose (2000 IU) corresponds to the upper limit of the Endocrine Society’s recommendations for adults at high risk for vitamin D deficiency. It was chosen on the assumption that early stage CRC patients who only recently underwent rehabilitation have a higher turnover of vitamin D metabolites than individuals from the general population [32]. Depending on the loading dose, overall doses will range between 168,000 and 566,000 IU vitamin D_3_ taken over 84 days.

#### *Control arm*

Patients will receive placebo in the same schedule as in the intervention arm.

#### *Compliance*

To ensure a high adherence to the trial protocol, all patients are thoroughly instructed orally at regular visits and in writing via the patient information documents. Daily intake of study medication and potential adverse events (AEs) are recorded in the patient diary. The participant can agree to receive a weekly SMS, reminding them to take their medication and fill in the diary. It will be allowed to take forgotten maintenance doses of the week on the day of the SMS reminder.

The investigator documents the supply of the trial medication as well as the return of unused loading dose capsules and/or empty packages. The coordinating center (Division of Clinical Epidemiology and Aging Research at the German Cancer Research Center, Heidelberg) keeps records of the return of unused maintenance dose capsules and/or empty packages. Intake of less than 80% of the trial medication will be defined as incompliance.

#### *Concomitant medication*

The treatment of accompanying illnesses is only accepted if they are not subject to the exclusion criteria and if they are not expected to affect the trial’s outcome measures or to interfere with the trial medication. All additional treatments taken by the participants at inclusion or at any time during the trial are considered concomitant treatments and will be queried in the questionnaires. The following concomitant medication is strictly prohibited: vitamin D and vitamin D analogs, cardiac glycosides, and high-dose calcium supplements (> 1000 mg calcium daily).

#### *Dose modification*

Dosage adjustments are not permitted during the trial. In the case of a diagnosed vitamin D_3_ overdose, the treatment will be stopped immediately.

#### *Randomization and blinding*

The pharmacy of the Heidelberg University Hospital manages randomization by assigning each medication package a unique three-digit number according to a randomization list. The list is created using the randomization software “RITA – Randomization in Treatment Arms” (Version 1.31) before the actual manufacturing of the study medication and is kept sealed at the coordinating center until completion of the trial. Thus, trial physicians, medical staff, patients, and staff of the coordinating center including biometricians and scientists are blinded throughout the trial. The drug packages will be sent to the trial sites in blocks of six with equal numbers of verum and placebo packages to ensure block randomization. Stratification by study center will be ensured. Trial physicians will assign the intervention blindly by taking the medication package next in row from the open block. In addition to the trial medication, the study sites will receive a sealed envelope for each randomization number with information on whether the corresponding drug package comprised verum or placebo. The envelopes will be kept at the respective study centers and remain closed, except in case of emergency unblinding due to safety reasons (e.g. safety parameters meet stopping criteria). While the trial is ongoing, the clinical monitor will check the presence and intactness of the envelopes regularly. After completion of the clinical trial, intentional unblinding is performed by combining the documentation at the trial sites with the information of the pharmacy’s randomization list.

For safety reasons, multiple laboratory tests have to be conducted in the course of the trial. In order to avoid accidental unblinding of the study staff at the trial sites and the coordinating center by knowledge of a patient’s serum 25(OH)D, serum calcium or urinary calcium levels, pseudonymized laboratory test results will be sent to a medical documentarist at the coordinating center who has no access to patient-identifying data or further pseudonymized research data collected within the trial. The medical documentarist will check the safety parameters and will inform the study sites if any of the stopping criteria are met.

### Study flow

The study flow is depicted in Fig. 1.

**Fig. 1 Fig1:**
[figure not shown]
Overview of the study flow. Abbreviations: *EORTC QLQ-FA12* European Organization for Research and Treatment of Cancer – Cancer related Fatigue; *EORTC QLQ-C30* European Organization for Research and Treatment of Cancer – Core Quality of life questionnaire with 30 items; *FACIT-F* Functional Assessment of Chronic Illness Therapy-Fatigue; *FACIT-F FWB* Functional Assessment of Chronic Illness Therapy-Fatigue – Functional Well-being; *GDS-15* Geriatric Depression Scale with 15 items; *UICC* Union for International Cancer Control

In total, 456 eligible CRC patients are being randomized in order to analyze 410 for the primary endpoint after an expected drop-out rate of 10%. The trial schedule is presented in Table 3.

**Table 3 Tab3:** Detailed schedule of all observations to be performed during the clinical trial

Procedure	Screening Visit for eligibility	Visit 1 Start of treatment	Visit 2 End of rehabilitation	Collection of data via questionnaire/ phone and blood/urine sampling by GP
Rehabilitation clinic	Admission	–	Discharge	–
Time-point of data assessment	–	Day 1	Day 12–21	Week 13–16
Planned doses of vitamin D_3_ per day	–	Individualized initial dose (20,000 or 40,000 IU, followed by 2000 IU per day) for day 1–11	Maintenance dose of 2000 IU per day for day 12–21	–
Inclusion/exclusion criteria	●	●		
Written informed consent	●			
Randomization		●		
Trial medication intake		●	●	
Subject diary regarding days of drug administration		●	●	
Physical examination (weight, height, waist circumference)	●			
Urinary pregnancy test for women of childbearing potential	●			
Assessment of CRC treatment	●			●
Concomitant diseases / Medical history	●			
Concomitant medication	●			●
Query about concomitant use of vitamin D_3_ or vitamin D analogs in self-medication in addition to trial medication				●
Fatigue	●			●
Functional well-being, QoL, infection frequency, and depression	●			●
Blood sampling for biomarker efficacy and safety endpoints	●		●	●
Urine sampling for safety endpoints	●		●	●
(S)AE recording and protocol deviations		●	●	●

Abbreviations: *CRC* colorectal cancer; *GP* general practitioner; *QoL* Quality of life; *SAE* Serious adverse event

During a first informative appointment, patients are briefed about the study and receive the printed study information. After having enough time to read the information materials, the potential study participants have the opportunity to ask questions before the official screening visit commences.

#### *Screening*

The trial physician will conduct the informed consent discussion with eligible patients and obtain the written informed consent. For each patient who agreed to participate in the trial, the coordinating center will generate a unique 4-digit patient identification number, which is being documented along with the date of enrollment in the patient identification list. The waist circumference of the patient will be measured. In order to calculate the BMI, the height and weight will be gauged additionally. Women of child bearing potential have to undergo a urine pregnancy test. All patients will be asked to complete a study questionnaire as well as to provide a blood and urine sample to gather baseline information.

#### *Visit 1 (start of the treatment phase, day 1)*

After checking the in- and exclusion criteria, eligible patients will be included in the clinical trial. The trial physician will hand out the trial medication to the participant for the first 28 days. This includes the entire quantity of capsules for the calculated loading dose and the amount of the daily maintenance dose that supplies the patient until visit 2 and one additional week to prevent any interruptions of the intervention. Along with the trial medication, participants will receive a patient diary in which the intake of medication and potential AEs during the upcoming treatment period of 12 weeks are recorded.

#### *Visit 2 (day 12–21)*

At the end of the stay in the rehabilitation clinic, the participants will have completed the intake of the loading dose. To check their compliance, the patients will be asked to bring the empty trial medication packages of the loading dose and any leftover medication to this visit. A blood and urine sample will be collected to monitor biomarkers and safety parameters including hypervitaminosis D, hypercalcemia, hypercalciuria, and renal dysfunction. All suspected cases of AEs reported by the participants are assessed by the trial physician. Once it is confirmed that none of the safety parameters meet any of the criteria for discontinuation, the patient receives the remaining trial medication for the days 29 to 84. If any clinically relevant abnormalities are detected, the intake of the trial medication will be stopped immediately and further measures initiated, as appropriate.

#### *13 to 16 weeks after beginning of treatment*

After finishing administration of the trial medication by the end of week 12, the participants will be asked to fill out a questionnaire to assess fatigue symptoms and further outcomes, and to provide a final blood and urine sample at their general practitioner’s (GP’s) office. The filled-in questionnaire will be sent back to the coordinating center along with the patient diary, the unused trial medication and the empty medication packages.

The coordinating center assesses the compliance, checks the plausibility of the questionnaire replies, and records potential AEs that were noted for the outpatient period in the patient diary. The study physician evaluates each AE for severity and a potential causal relationship to the trial medication. He/she further takes measures to treat and follow-up AEs as necessary. Cases of hypercalcemia and hypercalciuria detected during the final laboratory test will be followed up for additional 2 months after the last intake of the trial medication to monitor normalization of the albumin-corrected serum calcium and the urine calcium to creatinine ratio.

After reporting the end of the trial of a participant, the participant will be immediately unblinded by receiving information from the coordinating center on the treatment, the results of the latest 25(OH)D measurement, and on options to treat vitamin D deficiency. The participant can decide in consultation with his/her GP whether to start (for the placebo group) or continue (for the verum group) vitamin D_3_ supplementation. Unblinding will be performed for each participant separately by opening a sealed envelope with the patient’s randomization number and the information if the corresponding drug package contained verum or placebo. The unblinding will be done at the latest 5 weeks after week 16. To ensure the integrity of the data, staff members of the coordinating center will have clearly defined roles and tasks, which are assigned via a delegation log.

In order to collect questionnaires at the end of the intervention from almost all trial participants, they will be contacted several times: first by a mailed questionnaire and ultimately by a phone call. Furthermore, they will get a monetary compensation (25 € if the questionnaire is sent back or answered by phone and a blood sample was provided).

### **Data management**

Data handling will be described in the trial data management plan. The Coordination Center for Clinical Trials, Heidelberg (KKS) provides and monitors a validated electronic case report form (eCRF) for remote data entry. The eCRF will be used for all data entry by study centers and the coordination center. All entries in the eCRF will be verifiable by source documents (if not explicitly exempt from this rule) and include:
the randomization number (available once a patient is randomized),verification of compliance with in- and exclusion criteria,demographic data and data collected during the physical examination,concomitant diseases and medications,laboratory values,dates of participation in the study, of informed consent, and of dispensing study material and medication,AEs,date of drop-out and reasons for drop-out (voluntary information),and protocol deviations.

All patient data are documented pseudonymously. All documents and data pertaining to the trial will be stored at the study centers in the investigator site file (ISF) and at the coordinating center in the trial master file for at least 10 years after the end of the trial in accordance with the applicable regulations.

### Data collection and documentation by the trial sites

Written informed consent will be obtained for each participant before enrollment in the trial and will be kept in the ISF at the respective study centers. The investigators will enter the date and quantities of distributed and returned study medication as well as all participant data collected during rehabilitation into the eCRF, except biomarker results from the second blood and urine sample collection to avoid unblinding. All data entries in the eCRF will undergo an automatic online check for plausibility and consistency, which is defined in the data validation plan. In case of implausibility, a warning message will be produced during data entry. A responsible investigator or a designated representative will be obliged either to correct the implausible data or to confirm its authenticity and give an appropriate explanation. The responsible data manager will check all explanations and will resolve the warning if the explanation is appropriate.

The responsible investigator has to confirm the correctness of all entries in the eCRF with a dated electronic signature. The time points and frequency are pre-defined in the eCRF specification.

All missing data or inconsistencies will be reported back to the study centers and have to be clarified by the responsible investigator before database lock. If no further corrections are to be made in the database, it will be declared locked and can be used for statistical analyses.

### Data collection and documentation by the coordinating center

The coordinating center enters the pseudonymized laboratory results of the second and the final sample collection as well as study data from questionnaires and patient diaries in the eCRF. To ensure the integrity of the data, staff members of the coordinating center will have clearly defined roles and tasks which will be assigned via a delegation log. For example, coordinating center staff members who contact the study participants will not have access to the eCRF, the laboratory results or the sealed envelopes containing the information on the allocation of treatment. Staff members who open these envelopes or check the pseudonymized laboratory results of the study participants, in turn, will not have access to any patient-identifying data or other study data.

The data management will check the completeness, the validity, and the plausibility of the entered data using validation programs, which will generate queries where applicable. The head of the coordinating center or a designated representative will confirm the correctness of all entries in the eCRF by a dated signature as defined in the eCRF specification.

### Questionnaires

Each patient will complete a questionnaire in the rehabilitation clinic at baseline and in study weeks 13 to 16. The questionnaires will address lifestyle factors (smoking, alcohol consumption, diet, physical activity), CRC therapy (chemotherapy, radiotherapy, operation), and medical history (common diseases, family history of diseases) as well as the (validated) tools for assessment of the outcomes.

### Blood and urine sampling and laboratory measurements

Patients will be asked to provide a blood and a spontaneous urine sample upon screening (baseline), at the end of rehabilitation (day 12–21) and once again in the study weeks 13 to 16. The first two samples will be collected in the rehabilitation clinic (inpatient) while the final sample will be collected by the patient’s GP (outpatient). For the sampling at the GP’s office, the coordinating center will send pseudonymized sampling kits to the participants after trial week 12. One part of the samples will be used to determine biomarkers immediately (as efficacy or safety outcomes). Another part will be stored at the coordinating center for potential future post-hoc analyses with novel biomarkers.

All blood samples drawn during the trial will be either collected in clotting activator containing tubes to analyze serum or in EDTA tubes to analyze whole blood. The urine samples will be donated in a collection cup of 40 ml from which a volume of 10 ml is extracted using Urin-Monovette®, Luer, Germany. Any residual volume will be discarded. The quantity of collected blood and urine samples is shown in Table 4.

**Table 4 Tab4:** Time and volume of sampling

Setting	No. of sample	Phase of clinical trial	Blood Sampling		Urine Sampling
			EDTA tube	Serum tube	
Inpatient	1	Screening	1 × 2.6 ml	1 × 7.5 ml	1 × 10 ml
	2	Day 12 to 21	1 × 2.6 ml	4 × 7.5 ml	2 × 10 ml
Outpatient	3	Week 13 to 16	1 × 2.6 ml	1 × 7.5 ml, 3 × 9 ml	2 × 10 ml

**1st and 2nd sample**: The EDTA tube, one serum tube, and 10 ml urine will be prepared for transportation by the laboratories with which the rehabilitation clinics normally cooperate. This procedure ensures rapid transport and analysis of biomarkers within 48 h. The remaining samples (if any) will be sent via express mail to the coordinating center for aliquoting and storage at − 80 °C.

**3rd sample**: The GP will send all samples to the laboratory of the coordinating center via express mail. The latter will immediately send the EDTA tube, one serum tube, and 10 ml urine via express mail to the same cooperating laboratories that also process the first two specimens. The remaining samples will be stored at the laboratory of the coordinating center at − 80 °C. By using the same laboratories for the sample analysis, bias originating from different measurement methods is avoided.

To comply with the pre-analytical requirements, it is ensured that the transport time from sampling to analysis is less than 48 h and the temperature of the samples during transport is between 2 and 25 °C [36]. Serum tubes are inverted 3–5 times immediately after withdrawal and then stored at room temperature for 30 to 60 min to allow blood clotting. Tubes are subsequently centrifuged at 2500–3500 rpm for 10 min. EDTA tubes will be inverted eight to 10 times to ensure an even mixture of EDTA and blood.

The laboratories cooperating with the rehabilitation clinics will measure all parameters with standard state-of-the-art lab methods.

### **Safety assessment**

Participants will be asked about concomitant medication and diseases before inclusion. To minimize the risk of AEs and exacerbation of present conditions, patients will only be included if conditions that are listed as contraindications in the Summary of Product Characteristics of colecalciferol 20,000 IU or require special safety monitoring are not present (see exclusion criteria, Table 1). In the patient information document, patients will be informed about potential risks associated with the trial participation and instructed to contact the trial physician in case of serious medical problems. The observation period of AEs will begin with the first administration of the trial medication and end with its last administration. Events happening before the first administration are defined as medical history. AEs will be queried during every visit with the responsible investigator and additionally within the patient diary during the entire intervention phase. All AEs will be documented in the eCRF stating the participant’s randomization number, the start and end date, a description, the intensity, the seriousness, the relationship with the study medication, the measures taken, and the outcome.

All serious adverse events (SAEs) must be reported by the investigator to the pharmacovigilance department of KKS using a standardized form within 24 h after initial observation or awareness of the event. Every SAE will be subject to a second assessment by a designated person, who will be independent of the reporting investigator. All SAEs and their relevance for the risk-benefit assessment of the trial as well as the final report will be evaluated continuously during the trial.

A steering committee will be convened to ensure the ethical conduct of the trial and protect the rights as well as the welfare of the patients. The board consists of the coordinating investigator, the head of the coordinating center, the deputy head of the coordinating center, and the clinical pharmacology consultant. By periodically assessing the safety of the intervention and reviewing potential safety issues, amendments to the further trial conduct (modification, continuation, closure) will be decided and documented.

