**Infection frequency** will be assessed by a self-developed questionnaire. Participants will be asked to state the number of infection episodes for the following infections during the last 12 weeks: Infections of the upper and lower respiratory tract, gastrointestinal infection with diarrhea, cystitis, and fever higher than 38 °C. The total infection frequency will be the sum of all reported infection episodes. If this sum is lower than the number of stated fever episodes with ≥38 °C, the latter will be used as the total infection frequency. Endpoints will be the mean differences in infection frequencies (total, upper respiratory, and lower respiratory tract infections) between intervention and placebo group at trial week 13–16.

Finally, serum und urine parameters will be measured at every sample collection to evaluate the following secondary endpoints:
Mean difference in levels of total serum 25(OH)D between intervention and placebo group at trial day 12–21 and in trial week 13–16 as well as mean difference in change of levels of total serum 25(OH)D from baseline to trial day 12–21 and from baseline to trial week 13–16.Mean serum 25(OH)D levels > 50 nmol/L in intervention group at trial day 12–21 and in trial week 13–16.Mean differences in levels of biomarkers (white blood cell count (WBC), leukocyte subtype counts (band neutrophils, segmented neutrophils, eosinophils, basophils, lymphocytes, and monocytes), serum CRP, serum uric acid, serum creatinine, serum total cholesterol, serum LDL cholesterol, serum HDL cholesterol, and serum triglycerides between intervention and placebo group at trial day 12–21 and in trial week 13–16 as well as mean difference in change of levels of these biomarkers from baseline to trial day 12–21 and from baseline to trial week 13–16.Mean difference in HbA_1c_ levels between intervention and placebo group at trial week 13–16 as well as mean difference in change of HbA_1c_ levels from baseline to trial week 13–16.Differences in frequency of safety parameters (including hypervitaminosis D, hypercalcemia, hypercalciuria, and renal dysfunction (estimated glomerular filtration rate (eGFR) < 30 ml/min/1.73 m^2^) between intervention and placebo group at trial day 12–21 and in trial week 13–16.Mean differences in levels of safety parameters (including albumin-corrected serum calcium, urine calcium/creatinine ratio, and eGFR) between intervention and placebo group at trial day 12–21 and in trial week 13–16.

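### Adverse-event observation ends with the last capsule, so the window for clinical AEs and SAEs depends on when treatment stops and may differ between arms

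*Protocol article*

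**What the plan says.** The Safety assessment section fixes the AE window: "The observation period of AEs will begin with the first administration of the trial medication and end with its last administration". Events before the first dose are classed as medical history. Events after the last dose are given no status.

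Other parts of the protocol article bear on the same window:

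- **Treatment length.** The Intervention section sets 12 weeks (84 days) of study medication.
- **Early stopping.** Under Dose modification, if a vitamin D overdose is diagnosed, "the treatment will be stopped immediately". The visit 2 section also stops medication for clinically relevant abnormalities, and the blinding section describes stopping criteria based on safety parameters.
- **Sampling.** After screening, samples are taken "at the end of rehabilitation (day 12–21) and once again in the study weeks 13 to 16".
- **Diary.** The Safety assessment section has AEs recorded in the diary over the whole intervention phase. The visit 1 section gives the diary a 12-week treatment period. At week 13–16 the coordinating center takes outpatient AEs from it.
- **Schedule.** Table 3 marks (S)AE recording at visit 1, at visit 2 and at week 13–16.
- **Late laboratory findings.** "Cases of hypercalcemia and hypercalciuria detected during the final laboratory test will be followed up for additional 2 months" after the last intake.
- **Analysis.** Statistical methods has AEs and SAE frequencies analysed descriptively.

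**The concern.** An AE window that closes at the last dose is set by something that happens after randomisation and that treatment can cause. The stopping criteria rest on safety parameters such as hypervitaminosis D, hypercalcemia and hypercalciuria, which verum can be expected to raise. A patient stopped for such a finding would leave AE observation on the day of the last capsule, while a patient who tolerates treatment is observed for 84 days. If stops are more frequent on verum, that arm is observed for less time on average, and the loss falls on the patients whose later course matters most for safety.

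The plan itself expects some effects to outlast dosing, since it follows late hypercalcemia and hypercalciuria for two months. Yet a clinical event that begins a week after the last capsule is, on the stated rule, outside AE observation, and it is unclear whether the 24-hour SAE reporting duty applies to it. The AE and SAE tables will inform the benefit-risk statement. Post-treatment events that are not collected prospectively may not be recoverable later.

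**Working it through.** **Inputs**

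- Treatment period: 84 days (Intervention).
- Visit 2: day 12–21 (Table 3).
- Final assessment: week 13–16 (Table 3).
- AE window: first to last administration (Safety assessment).

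**The plan's own figure.** 12 weeks × 7 = 84 days, as stated. Week 13 begins on day 85 and week 16 ends on day 16 × 7 = 112.

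**Completers.** Uncovered time = day of final assessment − 84.

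- Earliest: 85 − 84 = 1 day.
- Latest: 112 − 84 = 28 days.

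**Patients stopped at visit 2.** This assumes that the last capsule is taken on the day of the visit.

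| Last dose | Days lost to day 84 | Share of 84 days | Days to start of week 13 | Days to end of week 16 |
|---|---|---|---|---|
| Day 12 | 84 − 12 = 72 | 72/84 = 86% | 85 − 12 = 73 | 112 − 12 = 100 |
| Day 21 | 84 − 21 = 63 | 63/84 = 75% | 85 − 21 = 64 | 112 − 21 = 91 |

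Each further day of dosing, for example while laboratory results are awaited, shortens the gap by one day. The first dispensed supply covers 28 days, and the remainder is released only once the visit 2 safety parameters are clear. If the whole first supply were taken as scheduled, the loss to day 84 would be 84 − 28 = 56 days (56/84 = 67%).

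Visit 2 is the relevant stopping point because it is the only scheduled safety sample during dosing. Stops triggered by scheduled laboratory tests will therefore cluster there.

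**Effect at arm level.** If a fraction *s* of an arm stops at visit 2 and everyone else completes, the mean on-treatment AE window in that arm falls by *s* × 75–86%. The difference between arms is (*s* on verum − *s* on placebo) × 75–86%. The documents give neither *s* nor an event rate after stopping, so the number of AEs missed cannot be calculated.

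**The passages side by side**

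- *Window against diary.* The window ends at the last administration. The diary runs for the intervention phase, described at visit 1 as 12 weeks. For a completer these coincide. For an early stopper they do not, and no rule says which governs.
- *Window against Table 3.* The (S)AE mark at week 13–16 falls after day 84. It could mean new events up to that contact, or collection of events already noted in the diary during treatment.

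**The case against.** The strongest reply is that the toxicities of main interest are captured elsewhere, and this is correct. A reader might infer that hypercalcemia, hypercalciuria or renal impairment found at week 13–16 drops out of the safety comparison. It does not. Outcomes and endpoints lists "Differences in frequency of safety parameters (including hypervitaminosis D, hypercalcemia, hypercalciuria, and renal dysfunction" as a between-group endpoint at day 12–21 and at week 13–16. It also lists "Mean differences in levels of safety parameters (including albumin-corrected serum calcium, urine calcium/creatinine ratio, and eGFR) between intervention and placebo group" at the same time points. Neither depends on the AE window, and dichotomous secondary endpoints get a chi-squared test. An abnormality that triggers a stop at visit 2 comes from a sample taken before the stop and is counted there.

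A reader might also infer that Table 3 flatly contradicts the Safety assessment section. The text does not force that reading. The week 13–16 section has the coordinating center take outpatient AEs from the diary, and the diary covers the treatment period, so the mark can mean late collection of on-treatment events. Two months of monitoring a laboratory value is likewise compatible with a window for AE onset.

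Third, the loss for early stoppers is not certain in practice, since nothing says that the diary ends at the stop. Fourth, selective under-counting on verum is not demonstrated: it needs stop rates by arm and event rates after stopping, and neither is given. AEs are analysed descriptively, so no AE hypothesis test is biased, and completers have the same rule in both arms.

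All of this narrows the point but does not remove it. The only explicit rule for clinical AEs and SAEs still ties their observation to the last dose, and the text that might soften it is ambiguous.

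**Conclusion.** The point holds for clinical AEs and SAEs. Their stated window varies with treatment duration. It closes 63–72 days (75–86%) before the planned end for a patient whose last dose is at visit 2, and 1–28 days before the final assessment for a completer. Under-counting on verum is possible, on the assumption that safety stops are more common there. That direction is an inference from what triggers a stop, and its size cannot be computed from the documents. The day counts assume that the literal rule is applied and, for early stoppers, that the last capsule is taken on the day of visit 2.

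The laboratory safety endpoints stand as planned. The window, the diary wording and the week 13–16 (S)AE mark are not in strict contradiction, but they leave each site to decide what counts after a stop and need to be reconciled.

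**What to change.** - State that AE and SAE observation runs, for every randomised patient, from the first dose to the week 13–16 assessment, whatever the date on which treatment stops.
- Report AE and SAE frequencies by arm over that common window. Flagging each event as before or after the last dose would keep an on-treatment table available.
- Extend the diary wording to match, and say that the Table 3 mark at week 13–16 covers all events up to that contact.
- Keep the two-month monitoring of hypercalcemia and hypercalciuria as follow-up of those cases, outside the between-arm AE comparison. Extending AE observation for those patients alone would again make the window depend on outcome, and it could run past individual unblinding, which follows once a participant's end of trial is reported.

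This changes data capture only and leaves doses and stopping criteria untouched. The week 13–16 contact and sample already exist, so the cost is protocol wording, with an amendment if one is needed, and up to four more diary weeks (112 − 84 = 28 days). The assessment date will still vary between patients by up to 112 − 85 = 27 days, but the end of the window will no longer be set by the date of treatment stop.
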